## Abstract

**Background:** Vaccine hesitancy is one of the greatest challenges to the success of coronavirus disease 2019 (COVID-19) vaccination campaigns. Videos promoting vaccines have a narrow scope focusing solely on facts, and less on the emotional and narrative elements of communication that can be equally persuasive. The role of humor, for example, has remained largely unexplored.

**Objective:** This study investigates whether theory-based videos can change people’s attitudes, beliefs, and intentions to receive the second COVID-19 vaccine. Our primary research question is: How do collectivistic and individualistic appeals, humor, and protagonist gender individually and jointly affect vaccination attitudes, beliefs, and intentions?

**Methods:** This project tapped into the underutilized Indian film industry—the world’s largest film producer—to promote vaccination messaging through short videos. Feedback from a community advisory board was utilized to inform the video scripts that were then shot by a production team. Eight videos were filmed and shared by adopting a 2 (appeal: individualistic or collectivistic) x 2 (tone: humor or non-humor) x 2 (protagonist gender: male or female) between-subjects design approach. Our sample includes Odia-speaking participants aged between 18 – 35 years old randomly assigned to watch one of the eight study videos. An online survey questionnaire, social media network analysis, and small group qualitative interviews will be utilized to explore how the entertainment-education videos can be used to reduce vaccine hesitancy.

**Discussion:** Vaccine messages do not fall into a cultural or cognitive vacuum. People process and make sense of information based on their prior experience, properties of the message, and their social environment. Yet, these considerations have taken secondary importance in vaccine communications. This research shows that it is possible to deliver high-caliber videos created in accordance with the audience's cultural and cognitive background.

**Conclusions: **This study will inform future health promotion messaging through brief videos on the internet.

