### Study setting

This research was conducted in the eastern Indian state of Odisha, with a population of about 46 million people
^
64
^. In 2011, 83.3% of the state lived in rural areas, and 16.7% of the population lived in urban areas
^
65
^. Additionally, 40% of the state’s population belong to Scheduled Tribes (22.85%) or Scheduled Castes (17.13%)
^
65
^. Odisha is also a state with relatively high levels of childhood immunization. Between 2019 and 2021, 91% of children between 12–23 months received all basic vaccinations against tuberculosis, diphtheria, pertussis, tetanus, polio, and measles and 98% of children between 12–23 months were at least partially vaccinated against the six major childhood illnesses
^
64
^. 

There have been 1 million confirmed cases and 8,400 deaths reported since the start of the COVID-19 pandemic in Odisha
^
66
^. Vaccine distribution in the country is decentralized, with each Indian state responsible for local administration and vaccination rates vary widely by state
^
67
^. As of February 2022, 95% of individuals over the age of 18 years had received the first dose, 92% were eligible for a second dose, and 80.3% of all eligible individuals had received both doses, making vaccination rates in Odisha higher than the national average (Express News Service, 2022). 

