### Study design

An online experiment was conducted through a 2 (appeal: individualistic or collectivistic) x 2 (tone: humor or non-humor) x 2 (protagonist gender: male or female) between-subjects design. Participants were recruited through a link posted on the Swasthya Plus Network (SPN) Odia website, and was shared by SPN on their public Odia WhatsApp channels. In order to be eligible for the study, participants needed to be between the ages of 18–35, and speak Odia. We did not check for language ability as the recruitment pages, channel, survey, and videos were all in Odia. Odia-speaking participants (N = 2,700) between the ages of 18–35 years were randomly assigned to watch one of the eight study videos, providing their vaccination attitudes, beliefs, and intentions both before and after viewing the videos. We tested for main effects of appeal, tone, and protagonist gender (as well as the underlying two-way and three-way interactions). During script development, we also sought the feedback from a community advisory board for cultural appropriateness. Videos were shot in December 2021 and the experiment itself was launched in January 2022.

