**a.   Consent**

Participants who clicked on the experiment link were then taken to the consent page, which asked for the participant’s age to determine eligibility. Although being able to speak Odia was an inclusion criterion, we did not need to ask about their language abilities because the questionnaire was conducted in Odia. If they did not meet the eligibility criteria, they were thanked and dismissed. In the consent form, the structure of the questionnaire and topics were outlined before each section. Additionally, participants were reminded that the questionnaire was voluntary and that they would receive a compensation of ₹200 (Indian Rupees) via google pay or phonePe, both digital wallets.

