**b.   Pre-exposure questions**

We started the survey by asking the respondents about their age, gender and their vaccination status. Participants who indicated that they had not received a COVID-19 vaccine were asked what their primary reason was for refraining from getting the particular vaccine. In an effort to understand attitudes and beliefs about COVID-19 vaccines (including vaccine hesitation towards COVID-19), participants were asked to rate their agreement on a series of statements adapted from Quinn
*et al*. (2019) on a five-point Likert scale from “strongly disagree” to “strongly agree”
^
10
^. Additionally, we asked how often and how likely specific COVID-19 thoughts had entered their minds in the last three months including the likelihood of contracting COVID-19 and the frequency that they thought about COVID-19 vaccinations. Finally, we included 13 questions about collectivism and individualism from Singelis
*et al*.’s 1995 vertical and horizontal collectivism and individualism scale
^
42
^. The three statements of each type of collectivism/individualism with the highest factor loadings along with one very culturally appropriate statement about family was included in the questionnaire.

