## Measurement

### Statistical analysis and power calculation

**Online experiment component:** We assumed that, prior to exposure, 30% of the population would be vaccine-hesitant and that exposure would affect the attitudes of 10% of the viewers. To achieve power of 80%, with an alpha of 5%, the required sample size would be 294 per group, which we rounded up to 300. To be able to conduct sub-analyses along caste (three subgroups) and three age groups (i.e., nine groups in total), the overall required sample size was calculated to be 2,700. 

**Data analysis**. Data analysis will be done in two phases. First, we will conduct manipulation checks for the three variables that were manipulated. We manipulated the scripts to have either an individualistic or a collectivistic appeal. Responses to questions that asked about the extent to which the videos had an individualistic appeal (coded as 1) or a collectivistic appeal (coded as 5) will be subjected to a t-test in which the assignment to condition (individualistic or collectivistic) will be the independent variable. Similarly, the extent to which the videos were perceived to be humorous will also undergo a t-test. Finally, we will ask participants to recall whether the main protagonist was a male or female. This will be compared against the assignment variable (whether assigned to the male or female protagonist) through a chi-square test. If the results of the two t-tests and the chi-square test are significant, we will deem the manipulations to have been successful. Second, we will run an analysis of covariance (ANCOVA) model in which assignment to experimental conditions will be the three independent variables (individualistic or collectivistic appeal; humor or serious tone; and protagonist gender) and attitudes toward vaccines will be the dependent variable. In this model we will control for demographic indicators. We will also test for three two-way and one three-way interactions among the independent variables.

**Qualitative component:** From the survey respondents (
*n*=2,700), we will identify the 10% (

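### Second-dose intention is named in the objective but no described model tests it, and it can be tested usefully only in respondents who have not had that dose

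*Protocol article*

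**What the plan says.** The Abstract states the objective as whether theory-based videos can shift three things: attitudes, beliefs and "intentions to receive the second COVID-19 vaccine". The primary research question that follows is broader: how the three message features "individually and jointly affect vaccination attitudes, beliefs, and intentions", with no mention of the second dose. Study design reports that attitudes, beliefs and intentions were collected both before and after the video.

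On entry, Study design says "participants needed to be between the ages of 18–35, and speak Odia". The Consent subsection describes a page "which asked for the participant’s age to determine eligibility". Vaccination status is not a criterion, although Pre-exposure questions says the survey began by "asking the respondents about their age, gender and their vaccination status".

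For Odisha in February 2022, Study setting gives 95% first-dose coverage in adults and 92% eligible for the second dose, and adds that "80.3% of all eligible individuals had received both doses". The Online experiment subsection reports 2,349 responses collected in that same month.

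Statistical analysis and power calculation describes one outcome model, an ANCOVA on the three manipulated factors and their interactions that controls for demographic indicators. In it, "attitudes toward vaccines will be the dependent variable".

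**The concern.** An objective that names three outcomes is followed by a model for one. Second-dose intention is the outcome closest to behaviour and to the Introduction's rationale, which is the gap between first and second doses. The article gives no analysis that would answer it.

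The obvious repair, running the same ANCOVA on intention in everyone, has its own difficulty. A person who already has the second dose cannot form a new intention to receive it. If most respondents are in that position and were still scored on the item, a message feature that moves the remaining people would appear as a small average effect. A null result could then be read as evidence that the feature does not work on the group the study had in mind.

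**Working it through.** **1. The plan's own sample size.** With 30% hesitant, a fall to 20%, two-sided 5% and 80% power:

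n = [1.960·√(2·0.25·0.75) + 0.842·√(0.30·0.70 + 0.20·0.80)]² / 0.10² = (1.200 + 0.512)² / 0.01 ≈ 293.2, so 294 per group.

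This reproduces the stated figure exactly. It concerns hesitancy and attitudes, not second-dose intention.

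**2. Share already fully vaccinated.** The denominators of the 92% and the 80.3% are not clear, so four readings are shown, each applied to 2,349 respondents. Those lacking dose 2 are 1 minus the fully vaccinated share. Those with one dose only are 0.95 minus that share.

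| Reading of the Study setting figures | Both doses | Lacking dose 2 | One dose only |
|---|---|---|---|
| 0.95 × 0.92 × 0.803 | 70.2% | 29.8% (700) | 24.8% (583) |
| 0.92 × 0.803 | 73.9% | 26.1% (614) | 21.1% (496) |
| 0.95 × 0.803 | 76.3% | 23.7% (557) | 18.7% (440) |
| 0.803 | 80.3% | 19.7% (463) | 14.7% (345) |

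The national figures in the Introduction (about 90% with one dose, about one in three of those without a second) give 0.90 × 2/3 = 60% fully vaccinated. So a majority had both doses on every reading. The two right-hand columns differ by the 5% with no dose, 0.05 × 2,349 ≈ 117 people.

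**3. Detectable main effect in each subset.** For one factor split evenly over n people, at 80% power and two-sided 5%, in SD units:

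d = 2 × (1.960 + 0.842)/√n ≈ 5.603/√n

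- Lacking dose 2: 5.603/√700 = 0.21 to 5.603/√463 = 0.26.
- One dose only: 5.603/√583 = 0.23 to 5.603/√345 = 0.30.

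No gain from adjusting for pre-exposure intention is included; adjustment would lower these values by an amount the article does not allow one to compute.

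**4. Illustration of averaging over everyone.** Assume a factor shifts intention by 0.25 SD in those lacking dose 2 and by nothing in the rest, with equal SDs. These values are assumptions and do not come from the article. With s the share lacking dose 2:

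- All respondents: power = Φ(0.25·s·√2349/2 − 1.96), which is 44% at s = 0.298 and 22% at s = 0.197.
- Only those lacking dose 2: power = Φ(0.25·√n/2 − 1.96), which is 91% at n = 700 and 77% at n = 463.

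**The case against.** The strongest reply is that nothing planned is diluted. The only model is on attitudes, the sample size rests on hesitancy, and the Vaccine hesitancy section treats hesitancy as a continuum on which people who accept a vaccine may still have concerns. Fully vaccinated respondents can therefore move on the planned outcome. Second-dose intention is one of three outcomes in the objective, and the primary research question is general, so open enrolment is a legitimate choice. All of this stands.

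It is also fair that the article does not say who received a second-dose intention item. Pre-exposure questions shows at least one item routed by status: only respondents reporting no vaccine were asked their reason. If intention was routed in a similar way, its analysis would already be restricted. The questionnaire is in the extended data and is not at hand. This makes the averaging problem conditional.

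A condensed article may also leave secondary models to a fuller plan, which may contain an intention model. But the article does more than stay silent: it states its outcome model, and that model covers only part of the objective it states.

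Finally, the 0.25 SD illustration follows from its assumptions and shows no defect by itself. That too is accepted.

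**Conclusion.** The point holds as a mismatch between objective and model. Second-dose intention is named as a target, the article describes no test of it, and the eligibility rule means a sound test needs a subset. Under the coverage figures quoted, that subset is roughly 460–700 of 2,349 if it is everyone lacking dose 2, or 350–580 if it is those with exactly one dose.

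A reader might go further and infer that most of the sample cannot respond, so the trial's planned effect is diluted or its sample size wrong. The documents do not support that. The inability to respond concerns second-dose intention alone, and neither the attitudes ANCOVA nor the 294 per group depends on it.

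The subset sizes assume that a self-selected online sample aged 18–35 mirrors statewide adult coverage; the respondents' actual vaccination status is not reported. The averaging problem further assumes that the intention item was put to everyone.

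**What to change.** Add one pre-specified ANCOVA of post-exposure second-dose intention, adjusted for pre-exposure intention, with the same three factors. Restrict it to respondents who reported before exposure that they had had one dose but not two. Report those with no dose separately, since their next decision is the first dose. State the actual subset size and its detectable effect. Status was asked before the video was assigned, so restricting on it keeps the randomised comparison intact.

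Keep attitudes in all respondents, with vaccination status added as a covariate.

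This needs status recorded by number of doses and a second-dose intention item asked before and after viewing; the article confirms neither in its item descriptions. If either is missing, reword the objective to attitudes toward vaccines in all comers.

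The cost is one extra model, on data already collected if those items exist. The downside is a smaller N and a wider detectable effect for intention, which should be stated openly.

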## Introduction

As the coronavirus disease 2019 (COVID-19) pandemic enters its third year, more than 315 million cases have been recorded and more than 5.5 million people have died worldwide
^
1
^. India has experienced the second-largest burden of COVID-19, with more than 40 million confirmed cases and nearly half a million cumulative deaths
^
2
^. Although the country was largely spared during the initial outbreak, a second wave' of the virus swept the country in spring 2021
^
3
^. With this surge, experts believe official statistics may have undercounted the true burden of the disease with a preliminary analysis of mortality rates suggesting as many as 3.97 million deaths occurring since the start of the pandemic
^
4
^.

India’s COVID-19 vaccination campaign was launched in January 2021 with an ambitious goal of fully immunizing all 1.3 billion Indian citizens against COVID-19 by the end of the year
^
5
^. The size of the population makes this campaign the world’s largest vaccination program
^
6
^. Initially, two vaccine products were authorized for use: Covishield produced by AstraZeneca and the locally-produced Covaxin, both requiring two doses administered 4 weeks (Covaxin) and 12–16 weeks (Covishield) apart
^
7
^. By the end of 2021, more than 1.5 billion doses of the COVID-19 vaccine had been administered, with an estimated 90% of the adult population having received one dose
^
5
^. However, among the vaccinated, roughly 1 in 3 had not received a second shot and were not fully protected
^
8
^. In addition, the demand for vaccines has declined since November 2021, the number of daily doses administered has tapered, with officials underscoring that decreased public demand as opposed to supply issues are driving the slowdown
^
5
^.

## Vaccine hesitancy

Globally, COVID-19 vaccination campaigns have been hindered by rising vaccine hesitancy, defined by the World Health Organization (WHO) as a “delay in acceptance or refusal of vaccination despite availability of vaccination services”
^
9
^. The WHO also describes major components that influence hesitancy, including: complacency, or the perceived need for vaccination; convenience, or the ease of obtaining a vaccine; and confidence, or the trust in the vaccine and the systems that produce and recommend it
^
9
^. Importantly, vaccine hesitancy is context specific, varying by population, region, and over time
^
9
^. In this conceptualization, instead of a binary defined by behavior, vaccine behavior and attitudes fall along a continuum, from active demand and acceptance to complete refusal
^
10
^. For instance, hesitant individuals may accept a vaccine but still harbor concerns, or intend to get a vaccine but delay initiation, while others may start a vaccine series but fail to complete all required doses. Although the dynamics of vaccine hesitancy in North America, Western Europe, and Australia have been well studied, comparatively little research has focused on vaccine hesitancy in Southeast Asia in general and India specifically
^
11,
12
^.

Pre-pandemic, India’s suboptimal vaccination rates were more often attributed to barriers to access, and not hesitancy
^
11
^. Recent examples can be tied to specific vaccines in discrete (and often marginalized) communities, including religious minorities, those living in slums, tribal populations, and those from scheduled castes
^
11,
13,
14
^. For instance, in the early 2000’s Larson
*et al*. documented resistance to polio vaccine campaigns led by international NGOs as rumors of vaccine-induced sterilization resonated with Muslim communities in a majority Hindu state
^
15
^. Unlike in the West, these isolated events have not coalesced into a recognizable “anti-vaccine” movement
^
11
^. Generally, vaccine acceptance has been high and the successes of the national Universal Immunization Program (UIP) in eliminating vaccine preventable childhood diseases has led to positive sentiment towards vaccines. It is important to note that prior to COVID-19 vaccines, no vaccines were authorized for universal administration to Indian adults, and available research on vaccine hesitancy is restricted mostly to parental hesitancy toward childhood vaccines
^
16
^. Further, given the large, dense population in India, even a small increase in vaccine hesitancy could result in a large unvaccinated population.

The COVID-19 pandemic along with the introduction of novel vaccines has also been linked to an “infodemic” where a deluge of health claims -- including those that are unverified, misleading, and outright false -- have complicated the health communication environment
^
17
^. Exposure to misinformation around COVID-19 and COVID-19 vaccines contributes to vaccine hesitancy, particularly as social media use has increased
^
18
^. Social media also allowed organized international anti-vaccine groups from the US and elsewhere to reach receptive Indian audiences
^
19
^. Access to multiple public platforms like Twitter and Facebook, and private or encrypted platforms like WhatsApp, has complicated researchers’ ability to effectively assess the impacts of vaccine misinformation
^
20
^. Indeed, little is known about the reasons why there is a hesitancy gap between the first and second vaccine doses.

Empirical data focused on Odisha, an Eastern state in India and our study setting, is limited. A 2020 survey relying on a small convenience sample (<400 people) by Panda
*et al*. (2021) found high confidence in COVID-19 vaccines and support for mandatory vaccination, but also found that respondents believed immunity from a naturally occurring infection would be more effective than vaccine-induced immunity
^
21
^. Data from the COVID-19 Symptom Survey suggests that early in the vaccination rollout, hesitancy was lower in Odisha than in many other Indian States, with less than 25% of respondents reporting unwillingness to get vaccinated
^
6
^. Traditionally, studies on vaccine communication have focused on several key communication elements such as the extent to which messages resonate with cultural values, how the messages are communicated (the appeal), and the source of the communication. However, vaccine hesitancy is context specific and has not been widely studied in India. Before structural and access-related issues can be addressed, we must first explore the social norms, influences and dynamics of vaccine hesitancy and complacency within India to see how they differ from the vaccine hesitancy literature that focus predominantly on North America and Western Europe. Thus, this paper focuses on social norms and cultural attitudes while exploring specifically how individualism-collectivism as the cultural factor; humor versus seriousness as the appeal; and gender as the key source characteristic are important to understand vaccine hesitancy.

## Role of humor

Health communication professionals designing vaccine promotion campaigns have to make decisions regarding the overall tone to adopt with campaigns focusing more on presenting facts and information, and less on the emotional and narrative elements of communication
^
22
^. The use of humor, in particular, has been largely overlooked.

Several studies have examined the use of humor by Indian youth as a coping mechanism, to navigate sensitive cultural normativity topics, and to enhance interpersonal relationships
^
23,
24
^. According to Hiranandani and Bing Yue (2014), humor is emphasized as an important element in Indian societies. In their study of humor styles among Indian university students, they found that the students use humor (‘mazaak’) to enhance social harmony, and that humor is “their preferred social interaction style and social influence of significant others” (p. 3). Hall (2019) indicates how mobile phones have been routinely used to spread jokes among hundreds of thousands of Indian mobile users. YouTube has been a primary platform for cultural expression, creativity, innovation and is a popular platform among Indian comedians
^
25–
28
^. In the study by Chaturvedi (2019), humor is one of the different elements used in a public health campaign in India aimed at mitigating the stigma of mental health through a series of YouTube videos
^
29
^. Ample research points to humor’s ability to gain attention, boost social influence, improve advertising and public relations campaigns, and facilitate strong communication between parties
^
30,
31
^. Moreover, in public service announcements (PSAs) and preparedness campaigns, humorous messages demonstrate an ability to enhance audiences’ attention and reduce counter-arguing through a light-hearted and likeable delivery of information
^
30
^. However, there is also the potential that humor may trivialize or otherwise hurt the perceived severity and credibility of the information being communicated, which may reduce an audiences’ intentions or likelihood to act on the information provided
^
30
^. For audiences in India specifically, humor has been credited in its ability to evoke an empathetic and understanding response in viewers
^
29
^. The few vaccine campaigns with a humorous twist are being appreciated and are popular on social media
^
32,
33
^.

 Observational studies from the COVID-19 pandemic also support this idea, with several content analyses of trending TikTok videos finding that humor is a dominant feature of content related to COVID-19 vaccines
^
34–
36
^. At the same time, humor has also been used to promote COVID-19 vaccine misinformation on the same platforms
^
35
^. There is considerable research complicating and contradicting the positive role of humor in health communication. Meyer and Venette explain that while potentially more memorable, using humor in health risk messages may mask or jeopardize the communication of serious health information, undermine the seriousness of the information, source credibility, and polarize or divide the audience
^
31,
37
^. In addition to the appropriateness and extent of humor used, different types of humor may differentially influence message perception. For example, Iles and Nan investigate the differences between sarcastic and ironic humor and found that both messaging styles reduced persuasiveness and increased counter-arguing—opposing earlier findings
^
30,
37,
38
^. The challenge for health communicators is not only the choice of tone (factual vs. humorous) but even more complex—what kind of fact(s) and what kind of humor makes for effective messaging for a specific context and audience.

